## Abstract

**Background:**

Safe, highly curative, short course, direct acting antiviral (DAA) therapies are now available to treat chronic hepatitis C. DAA therapy is freely available to all adults chronically infected with the hepatitis C virus (HCV) in Australia. If left untreated, hepatitis C may lead to progressive hepatic fibrosis, cirrhosis and hepatocellular carcinoma. Australia is committed to eliminating hepatitis as a public health threat by 2030 set by the World Health Organization. However, since the introduction of funded DAA treatment, uptake has been suboptimal. Australia needs improved strategies for testing, treatment uptake and treatment completion to address the persisting hepatitis C public health problem. PLATINUM C is a HCV treatment registry and research platform for assessing the comparative effectiveness of alternative interventions for achieving virological cure.

**Methods:**

PLATINUM C will prospectively enrol people with active HCV infection confirmed by recent detection of HCV ribonucleic acid (RNA) in blood. Those enrolled will agree to allow standardised collection of demographic, lifestyle, treatment, virological outcome and other relevant clinical data to better inform the future management of HCV infection. The primary outcome is virological cure evidenced by sustained virological response (SVR), which is defined as a negative HCV PCR result 6 to 18 months after initial prescription of DAA therapy and no less than 12 weeks after the completion of treatment. Study participants will be invited to opt-in to medication adherence monitoring and quality of life assessments using validated self-reported instruments (EQ-5D-5L).

**Discussion:**

PLATINUM C is a treatment registry and platform for nesting pragmatic trials. Data collected will inform the design, development and implementation of pragmatic trials. The digital infrastructure, study procedures and governing systems established by the registry will allow PLATINUM C to support a wider research platform in the management of hepatitis C in primary care.

**Trial registration:**

The trial is registered with the Australia and New Zealand Clinical Trials Register (ACTRN12619000023156). Date of registration: 10/01/2019.

**Supplementary Information:**

**Supplementary information** accompanies this paper at 10.1186/s12879-020-05531-4.

## Background

### Hepatitis C in Australia

Hepatitis C virus (HCV) infection is a major public health issue in Australia and other countries due to the substantial morbidity associated with chronic infection. It is estimated 71 million people are living with HCV worldwide including over 180,000 in Australia [1, 2]. Those chronically infected with HCV, if left untreated, are at risk of progressive hepatic fibrosis, cirrhosis and hepatocellular carcinoma.

With the recent development of direct acting antiviral (DAA) therapy, HCV infection is now curable in the majority of those infected with drugs that are safe, well tolerated, and highly effective. In response the World Health Organization called for the elimination of hepatitis C as a public health threat and set targets to reduce HCV-related mortality by 65% and HCV infection incidence by 80% by 2030 [3].

Australia was one of the first countries globally to make treatment available for all. From March 2016, all adults chronically infected with HCV in Australia have been eligible for treatment with DAA funded by the Government under the Pharmaceutical Benefit Scheme (PBS). Implementation of DAA therapies has led to a shift of HCV management from specialised tertiary care to the primary care setting. Initially, prescribing the newly licenced DAAs was complicated by the number of drugs available and treatment guidelines that factor in virus genotype, cirrhosis status, previous treatment status, drug-drug interactions and presence of comorbidities.

If the WHO elimination targets are to be met, effective strategies are needed to increase the number of people being tested, treated and cured [4]. These strategies are still largely unknown. Those most affected by HCV infection are often those who are relatively under-served by, or who have difficulties accessing, health care [5]. This includes people who inject drugs, incarcerated populations, people in rural and remote settings, Indigenous and migrant populations [6, 7].

### Aim

The overall aim of the PLATINUM C treatment registry is to inform the improved management of HCV in primary care. It is envisioned that this will provide a research platform to enable the embedding of pragmatic trials. This protocol outlines the background, objectives, endpoints, data collection and study procedures generic to this research platform and sets out the purpose and rational for establishment of the treatment registry.

## Methods/design

### Study design

This study is a prospective, multi-site treatment registry of primary care practices within Australia. Individual participation in the PLATINUM C research platform involves the capture of consenting participants’ demographic and clinical data and HCV treatment and outcome data. This information will be used to compare treatment response rates in different subgroups of patients. Where important variation in practice and outcomes are identified, this data will be used, as part of a research prioritisation process, in consultation with the Platinum C Community Reference Group to inform the design, development and implementation of pragmatic trials involving randomised assignment of alternative treatment options.

### Study population and setting

PLATINUM C will enrol adults (≥ 18 years) who have confirmed active HCV infection (positive HCV RNA PCR within 3 months) from community primary health care clinics which are involved in delivering HCV infection care. Ethical approval has been obtained for 5 high caseload primary health care clinics across metropolitan Perth, Western Australia, where the underlining chronic HCV prevalence ranges between 0.66–0.68%. Additional study sites across Australia, where the national prevalence was estimated to be 0.78% at the start of 2016, will be included with ethical permission as the study progresses [8]. Participating clinics will agree to comply with study procedures including the embedding of the data collection and prescribing tools within their clinical practice.

### Objectives

The primary objective of PLATINUM C is, for adults with chronic HCV infection, to determine the absolute and comparative effectiveness of a range of interventions to achieve a HCV virological cure. This is demonstrated by a sustained viral response (SVR), defined as an undetectable HCV ribonucleic acid (RNA) ≥12 weeks after discontinuation of antiviral treatment and within 18 months of the start of treatment. Interventions will include licenced and funded DAA therapies and other management strategies to be defined by platform embedded trials.

The secondary objectives are to describe chronic HCV management in primary care for different patient subgroups, including by: (i) describing the distribution of the treatment response under alternative management options, (ii) characterising treatment adherence, (iii) identifying demographic and clinical characteristics associated with high risk of lost-to-follow-up from standard care, and (iv) describing and comparing patterns of health care utilisation.

### Outcomes

The primary outcome is virological cure as evidenced by the endpoint of sustained virological response (SVR) defined as a negative HCV RNA (in plasma) PCR result 6 to 18 months after the initial prescription of DAA therapy and no less than 12 weeks after the end of antiviral treatment.

Secondary outcomes and endpoints are:
(i)Completion of follow up defined by the completion of SVR12 testing (HCV RNA PCR)(ii)Adherence of study participants to antiviral treatment recorded as the self-reported proportion of total prescribed doses taken,(iii)Quality of life, as measured by the self-reported EQ-5D-5L questionnaire administered during and for up to 24 months after initiation of treatment and,(iv)Healthcare utilisation defined as any attendance for healthcare related service that attracts a cost to the individual, insurer or government.

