#### Data collection

Relevant data (outlined in Table 1) will be obtained directly from the healthcare providers and participants. Data will be collected through data capture and prescribing tools and phone and/or email participant surveys.

**Table 1 Tab1:** Summary of data collection

Data type	Information recorded	Time point
Demographics	Age, gender, postcode, Indigenous status	Enrolment
Lifestyle	Self-reported injecting drug use, self-reported alcohol in-take, self-reported housing status, self-reported reuse of a needle/syringe, self-reported prescribed opioid substitution therapy, risk of treatment disruption (including imprisonment)	Enrolment
Clinical	Hepatitis C history, previous treatment, comorbidities, HCV genotype and RNA level, liver function tests, liver fibrosis assessment	Treatment prescription
Treatment	DAA therapy and duration prescribed, treatment setting, type of prescriber, concurrent medication, other concurrent HCV management interventions	Treatment prescription
Medication adherence	Self-reported adherence to therapy	Weekly during treatment course
Quality of life	Self-reported quality of life (QoL) score (EQ-5D-5L)	0, 3, 6, 12 and 24 months after treatment initiation
Outcomes	HCV RNA PCR, all re-collected laboratory and imaging results, self-reported injecting drug use,	3 months after treatment completion

PLATINUM C will use a direct data capture tool that is integrated with the practice software (described in Fig. 1). Data from consenting participants will be extracted and uploaded to the data capture system. Information unable to be extracted with be uploaded by the consulting practitioner. The data capture tool will ensure all information required for prescribing DAAs or referral for specialist consultation is collected. The data capture tool will also serve to provide prescribing recommendation based on the Australia recommendation for genotype, cirrhosis level and treatment experience. Patient information collected will be stored within the practice software and de-identified participant information will be fed directly into a secure online database via secure middleware. A monitoring dashboard will allow healthcare staff to track when participants are due for follow-up SVR12 testing and long-term cirrhosis assessments.

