#### Data analysis

Primary analyses of all data will use the intention-to-treat (ITT) principle. Demographic, clinical and other baseline variables will be summarised by viral genotype, liver cirrhosis status, previous HCV treatment and clinician prescribed treatment. Continuous variables will be summarised as mean and standard deviation for symmetric distributions and median and interquartile range (IQR) for asymmetric distributions. Categorical variables will be summarised at each level as frequency and percentage. Frequencies below five will be reported as “< 5” to protect individual confidentiality.

For the primary endpoint a Bayesian logistic regression model, with weakly informative priors, will be used to compare treatment groups and incorporate Bayesian borrowing across pre-specified subgroups. The exact model will depend on the trial modules (and interventions) defined and will be documented in the statistical analysis plan (SAP). The proportion of participants that achieve SVR12 will be reported every 200 participants. Secondary endpoints will be similarly summarised and analysed using Bayesian regression models, which will be documented in the SAP.

Self-reported DAA treatment adherence will be summarised as the median (and IQR) proportion of prescribed doses taken in weeks 1 to 12 by viral genotype, liver cirrhosis status and clinician prescribed treatment. Self-reported quality of life measured during and for up to 24 months after initiation of treatment, as measured by the EQ-5D-5L, will be summarised by median (and IQR) by viral genotype, liver cirrhosis status and clinician prescribed treatment.

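### The primary SVR endpoint is defined in two incompatible ways, and its 6-month floor from prescription can exclude a negative PCR taken on the plan's own schedule, depending on course length

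*Protocol article*

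**What the plan says.** The protocol article describes the primary endpoint or its measurement in five places.

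- **Outcomes:** "a negative HCV RNA (in plasma) PCR result 6 to 18 months after the initial prescription of DAA therapy". A second condition, a minimum of 12 weeks off treatment, is joined to this one, and both must hold.
- **Abstract, Methods:** the same two conditions, "6 to 18 months after initial prescription of DAA therapy and no less than 12 weeks after the completion of treatment".
- **Objectives:** "undetectable HCV ribonucleic acid (RNA) ≥12 weeks after discontinuation of antiviral treatment and within 18 months of the start of treatment". There is no 6-month floor, and the 18-month limit runs from treatment start instead of prescription.
- **Data collection:** Table 1 places the outcome PCR "3 months after treatment completion". The text below it describes a dashboard with which staff "track when participants are due for follow-up SVR12 testing".
- **Data analysis:** "The proportion of participants that achieve SVR12 will be reported every 200 participants".

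Secondary outcome (i) treats follow-up as complete once the SVR12 test has been done. SVR12 has no separate definition in the article; I read it as testing 12 weeks after the end of treatment.

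**The concern.** The definitions differ in their lower bound and in their time origin, so the same test result can be classified differently depending on which section is applied. The schedule makes this a practical matter. Testing is timed from the end of treatment, whereas the floor is timed from prescription. A person on a short course who is tested when the dashboard says so may have a valid negative result that comes too early for the Outcomes definition.

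The primary objective covers both the absolute cure rate and comparisons between interventions, including DAA therapies, and Table 1 records the prescribed duration. If whether an on-time test counts depends on course length, regimens of different length have different chances of a countable negative for reasons unrelated to cure. That would lower the apparent SVR and tilt the comparison against shorter courses.

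**Working it through.** The article states no figure for this, so there is none to reproduce. The check is calendar arithmetic.

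**Inputs**
- Window opens (Outcomes): 6 months after prescription, 365.25/2 = 182.6 days.
- Test time: 12 weeks after treatment (SVR12 prompt) = 84 days, or 3 months (Table 1) = 365.25/4 = 91.3 days.
- Course length w, in weeks: not stated. Twelve weeks is inferred from the adherence summary in Data analysis, "the median (and IQR) proportion of prescribed doses taken in weeks 1 to 12". Lengths of 8, 16 and 24 weeks are assumptions to show the range.
- Lag L from prescription to first dose: not stated; 0 in the base case.

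**Formula**

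Test day from prescription = L + 7w + 84, or L + 7w + 91.3. Gap = 182.6 − test day; a positive gap means the test is too early.

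**Results with L = 0.** The calendar range uses true calendar months over every prescription date from 2019 to 2022.

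| Course | 12-week test: day | Calendar range | 3-month test: day | Calendar range |
|---|---|---|---|---|
| 8 wk (assumed) | 56 + 84 = 140 | 41–44 days early | 56 + 91.3 = 147.3 | 33–37 days early |
| 12 wk (inferred) | 84 + 84 = 168 | 13–16 days early | 84 + 91.3 = 175.3 | 5–9 days early |
| 16 wk (assumed) | 112 + 84 = 196 | 12–15 days inside | 112 + 91.3 = 203.3 | 18–23 days inside |
| 24 wk (assumed) | 168 + 84 = 252 | 68–71 days inside | 168 + 91.3 = 259.3 | 73–79 days inside |

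**Break-even points**
- Shortest course whose scheduled test reaches the window with no delay: (182.6 − 84)/7 = 14.1 weeks for the 12-week test; (182.6 − 91.3)/7 = 13.0 weeks for the 3-month test.
- Start lag plus lateness of testing needed to reach the window: 5 to 16 days after a 12-week course, 33 to 44 days after an 8-week course.

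Twelve weeks (84 days) is shorter than any three calendar months. Twelve weeks of treatment plus three months is therefore always less than six months from treatment start.

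**One test under each definition.** Take a 12-week course started on the day of prescription, with a negative PCR on day 175, which is 175 − 84 = 91 days after stopping.
- Objectives: 91 ≥ 84 and well inside 18 months, so cured.
- Secondary outcome (i): SVR12 test done, so follow-up complete.
- Data analysis: counted in the SVR12 proportion, on the reading of SVR12 given above.
- Outcomes and Abstract: the 12-week condition is met, but 175 < 182.6, so the primary outcome is not met on this test.

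The upper limit differs too. Eighteen months from treatment start ends L days later than 18 months from prescription.

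**The case against.** Several points on the other side are sound.

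- **The 12-week case is marginal.** A reader might infer that an on-schedule PCR after 12 weeks or less can never count. The document does not support that. The window runs from prescription, so any delay in starting moves the test towards it, and Table 1 gives a nominal time in routine care. One to two weeks of combined slippage is enough after a 12-week course.
- **Later tests count.** A negative PCR up to 18 months still qualifies. However, the article schedules no further PCR for someone already tested, and its Limitations section expects losses to follow-up, so a later test cannot be relied on.
- **Course lengths are not stated.** Only 12 weeks has any anchor in the text. The wide 8-week gap and the 16- and 24-week contrast are assumptions.
- **Handling of early negatives is not stated.** A reader might infer that they are scored as failures because the primary analysis is by intention to treat. The article does not say so, and such a rule may sit in the SAP.
- **No size can be given.** It is tempting to multiply an assumed cure rate by an assumed share of tests that are not on schedule. That only returns the inputs, and it treats every on-time test as lost, which the table contradicts.
- **The bias is conditional.** It needs compared groups with different course lengths, and the trial modules are not yet defined.
- **The floor may have a purpose.** Table 1 lists prescribed duration but no actual stopping date, and weekly adherence reporting is opt-in. A bound counted from prescription could guard against uncertain end dates, although the article gives no such rationale.

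These points limit the strength of the claim. They do not remove the conflict between Objectives and Outcomes, which depends on no assumption about course length, lag or repeat testing. It is also not a detail left to the SAP, because no SAP can agree with both definitions.

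**Conclusion.** The concern holds as a conflict in the primary endpoint definition, joined to a test schedule that can miss the stricter definition's window. With same-day start, the scheduled test after a 12-week course falls about 5 to 16 days early. After an assumed 8-week course it falls about 33 to 44 days early, and after assumed 16- and 24-week courses it falls inside. Read literally, this can understate SVR and can bias comparisons between regimens of different length.

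The effect on the SVR estimate cannot be quantified. It depends on the mix of course lengths, the lag from prescription to first dose, how punctual testing is, how often tests are repeated and how early negatives are handled, and the article gives none of these.

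**What to change.** Use one SVR definition, with one stated time anchor, in the Abstract, Objectives, Outcomes, Data collection (Table 1 and dashboard) and Data analysis, and state that SVR and SVR12 mean the same endpoint if that is intended.

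The simplest version drops the 6-month lower bound, as the Objectives already do: HCV RNA negative at least 12 weeks after the end of treatment and no later than 18 months after the chosen anchor. On-schedule tests after 8- or 12-week courses (days 140 to 175 in the table) would then qualify.

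If a floor from prescription is kept, for example because actual stopping dates are uncertain, give that reason and align the scheduled test time and dashboard prompt with the floor.

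Removing the floor is a wording amendment only, with no extra visits or participants. Its downside is losing any safeguard the floor gave where the end-of-treatment date is not recorded. The change should be made before the definition is applied to outcome data.

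### The primary SVR definition is not tied to the first DAA course, so cure after retreatment can be credited to a failed first regimen, and an on-time negative test can fall before the window opens

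*Protocol article*

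**What the plan says.** The Protocol article describes the endpoint and its timing in several places.

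- **Outcomes** (and, in near-identical terms, the Abstract): the endpoint is a negative plasma PCR "6 to 18 months after the initial prescription of DAA therapy and no less than 12 weeks after the end of antiviral treatment".
- **Objectives:** the aim is "to determine the absolute and comparative effectiveness of a range of interventions to achieve a HCV virological cure". SVR is described there as undetectable RNA "≥12 weeks after discontinuation of antiviral treatment and within 18 months of the start of treatment". The clock starts with treatment rather than prescription, and there is no 6-month lower bound.
- **Data collection, Table 1, Outcomes row:** the items are "HCV RNA PCR, all re-collected laboratory and imaging results, self-reported injecting drug use", scheduled at "3 months after treatment completion".
- **Data analysis:** primary analyses follow ITT, treatment groups are compared on the primary endpoint by Bayesian logistic regression, and the proportion with SVR12 is reported every 200 participants. The exact model is left to the SAP.

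No section says which result counts when several fall in the window, how a second course is classified, or how reinfection is told apart from relapse.

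**The concern.** SVR at 12 weeks is ordinarily a property of one treatment course. Here the window opens and closes relative to the first prescription, while the 12-week condition refers to antiviral treatment in general. Applied literally, a patient whose first regimen failed, who was retreated and who then tested negative before month 18 satisfies both conditions. If patients are analysed by the regimen first prescribed, that success belongs to the regimen that did not work. A less effective regimen has more failures to rescue, so it gains more, and the contrast shrinks.

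The second issue is the lower bound. A negative test taken on the Table 1 schedule may come too early to count. If the patient is then reinfected before another test, the only in-window result is positive and a cured patient is scored as a failure. The outcome then depends on when the test was done as well as on the regimen. The Background names people who inject drugs among those most affected, and Limitations expects loss to follow-up, so uneven test timing is foreseeable.

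This definition is generic to the platform, and the Discussion says that randomised modules will extend this core protocol. A loose definition may therefore carry over into them.

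**Working it through.** The document gives no cure, retreatment or reinfection rates and no sample size, so there is no stated figure to reproduce. One month is taken as 365.25/12 = 30.44 days; 6 months = 182.6 days and 18 months = 547.9 days.

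**1. Does a second course fit?** The 12-week course length (84 days) is an assumption, suggested by the adherence summary, which uses the "proportion of prescribed doses taken in weeks 1 to 12". Treatment is taken to start at prescription.

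Earliest qualifying test after retreatment = first course + 84 days + gap + second course + 84 days.

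| Gap | Second course | Days | Months | Within 18 months? |
|---|---|---|---|---|
| 0 | 12 weeks | 84+84+0+84+84 = 336 | 11.0 | yes |
| 13 weeks | 12 weeks | 336+91 = 427 | 14.0 | yes |
| 26 weeks | 12 weeks | 336+182 = 518 | 17.0 | yes |
| 13 weeks | 24 weeks | 427+84 = 511 | 16.8 | yes |
| 26 weeks | 24 weeks | 518+84 = 602 | 19.8 | no |

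Retreatment fits comfortably in most of these cases.

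**2. How much could this shrink a difference?** Let p be the first-course cure rate, q the share of failures retreated and tested again in time, and c the retreatment cure rate. Observed SVR = p + (1 − p)·q·c. With the same q and c in both groups, the observed difference = (true difference) × (1 − q·c). All rates are assumed: p = 95% and 90%, c = 95%.

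- q = 30%: 5 × (1 − 0.285) = 3.6 points
- q = 50%: 5 × (1 − 0.475) = 2.6 points
- q = 80%: 5 × (1 − 0.76) = 1.2 points

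**3. Does the scheduled test fall inside the window?** Counted from treatment start:

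- 12-week course, test at exactly 12 weeks: 84 + 84 = 168 days = 5.5 months
- 12-week course, Table 1 test: 84 + 91.3 = 175.3 days = 5.8 months
- 8-week course (assumed), Table 1 test: 56 + 91.3 = 147.3 days = 4.8 months

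All fall before 182.6 days. Because the bound in Outcomes runs from prescription, a delay between prescription and first dose moves the test toward the window. For the 12-week course, 182.6 − 175.3 = 7.3 days of delay would be enough.

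**4. How much does test timing matter if there is only one test?** Assume 95% cure, a 12-week course and a constant reinfection rate λ after treatment ends. Observed SVR = 0.95 × exp(−λt), with t = (182.6 − 84)/365.25 = 0.27 years for a test at month 6 and t = (547.9 − 84)/365.25 = 1.27 years at month 18.

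| Assumed λ per 100 person-years | Sole test at month 6 | Sole test at month 18 |
|---|---|---|
| 1 | 94.7% | 93.8% |
| 5 | 93.7% | 89.2% |
| 10 | 92.5% | 83.7% |
| 20 | 90.0% | 73.7% |

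These figures apply only to patients with no earlier qualifying negative.

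**The case against.** The strongest reply is that the document, read as a whole, describes one course and one planned test. Objectives speaks of starting and stopping treatment, Table 1 has a single outcome time point, and the text refers to SVR12. On that reading, crediting a second course is permitted by loose wording but not prescribed. This stands, and the point should be put that way: a reader might infer that the protocol intends to credit retreatment, but no sentence says so.

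It can also be said that derivation rules belong in the SAP, which is not shown. That is fair for the model and for missing data. The endpoint definition, however, is stated here, and its wording is what admits the second course.

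A third reply is that cure by 18 months, whatever follows the first prescription, is a coherent treatment-policy outcome for a platform interested in real-world effectiveness. It is coherent, but the document does not claim it, and it is a different quantity from course-specific SVR12.

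Two stronger readings should be resisted. The definition does not accept any negative result within 18 months: the test must fall in months 6 to 18 and at least 12 weeks after treatment. Nor does late reinfection generally count as failure: a patient with a qualifying negative at month 7 and reinfection at month 12 has already met the endpoint.

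**Conclusion.** The concern holds in a limited form. Applied as worded, and with ITT comparison of treatment groups, the endpoint lets cure after a second course count for a first regimen that failed. For 12-week courses with gaps of 0 to 26 weeks, the timing allows this at about 11 to 17 months. The effect is to attenuate differences between regimens. The fall from 5 points to 3.6, 2.6 or 1.2 is arithmetically right but rests wholly on assumed rates. It shows sensitivity and does not forecast this registry's results; the 80% case in particular needs most failures to be retested, retreated and tested again in time.

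Misclassification through reinfection is narrower. It occurs only when no qualifying negative comes first, either because the sole test is late or because the on-time test preceded the 6-month bound. Outcomes, Objectives and Table 1 do disagree on the time anchor and the lower bound, and this needs no assumed rates to see. The change should be made before modules inherit the definition.

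**What to change.** Reword the primary endpoint and add a short derivation rule:

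1. Define primary SVR by the first PCR taken at least 12 weeks after the end of the first prescribed course and within 18 months of the start of treatment.
2. Reconcile Objectives, Outcomes and Table 1 on the time anchor, and drop the 6-month lower bound so that an on-time test counts.
3. Classify a second course started before a qualifying negative as non-SVR for the first course.
4. Record a positive after a qualifying negative as recurrence or reinfection, without changing SVR.
5. Report cure by 18 months including retreatment as a separate secondary outcome, which keeps the treatment-policy question.
6. Report the timing of the qualifying test by treatment group.

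The cost is wording and programming. The headline cure proportion may be slightly lower. Second-course start dates must be taken from the prescribing records, since Table 1 does not list them explicitly. One limitation remains: a first test taken late still cannot separate reinfection from relapse, which is why item 6 is needed. None of this affects how patients are treated.
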